# Effectiveness of yoga therapy as an adjunct on mental health status, quality of life, and medication adherence among people living with HIV on antiretroviral therapy: A study protocol of a randomized controlled trial (ART YOGA)

**DOI:** 10.1371/journal.pone.0331992

**Published:** 2026-04-27

## Abstract

**Introduction:**

Human Immunodeficiency Virus, the retrovirus that causes Acquired Immune Deficiency Syndrome, is a major global public health threat. This chronic viral infection diminishes the immune system by attacking CD4 cells. The principal treatment is antiretroviral medication (ART), which significantly increases the life expectancy of HIV patients. However, ART does not address psychological issues, including depression, anxiety, and stress. Psychosocial factors are known to influence HIV disease progression through activation of stress-related biological pathways, including the hypothalamic–pituitary–adrenal (HPA) axis, inflammatory cytokine responses, and monoamine neurotransmitter dysregulation. Mind–body practices such as yoga may modulate these pathways by reducing physiological stress, improving emotional regulation, and enhancing overall well-being. The current trial aims to assess the effectiveness of yoga as an adjunct therapy on psychological parameters (depression, anxiety, and stress), quality of life, and medication adherence of people living with HIV on antiretroviral therapy at a tertiary care hospital in AIIMS, New Delhi, India.

**Materials and methods:**

This study is a two-arm, parallel-group, open-label, blinded-endpoint, single-center, randomized controlled trial investigating the effects of a yoga therapy as an adjunct therapy in people living with HIV (PLHIV). Participants (n = 192) will be randomized to either 12 weeks of a Yoga therapy program (n = 96) or an Active control group, i.e., a prescribed brisk walk (n = 96). Both groups will receive standard treatment. The primary outcome is anxiety and depression scores (HADS-A and HADS-D), and the secondary outcomes are Stress (PSS), quality of life (WHOQOL-HIV BREF and SF-36 QoL), and medication adherence.

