## Materials and methods

### Trial design

We propose a two-arm, parallel, prospective, randomized, open-label, blinded-endpoint trial with four assessment points: baseline, 3 months, 6 months, and 12 months. The study protocol has been developed in compliance with the Standard Protocol Items: Recommendations for Interventional Trials (SPIRIT) checklist (see S1 SPIRIT Checklist), and the SPIRIT schedule for the study is presented in Fig 1, including the screening, enrolment, and follow-up visit timelines [25]. The CONSORT flow diagram of the study protocol is shown in Fig 2. A visual abstract summarizing the study design is provided in Fig 3. The total study duration is 3 years, including 1 year of follow-up.

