#### Description of the outcome measures.

The study will begin with a baseline screening visit, during which written informed consent will be obtained before starting any additional study activity. Clinical assessment, medical history, demographic characteristics, and questionnaire data will be collected at baseline and at the 3rd, 6th, and 12th-month follow-up visits. After being fully rested, all assessments will be conducted in the following order: heart rate, blood pressure, body composition, and questionnaires (Hospital Anxiety and Depression Scale (HADS), WHOQOL-HIV BREF, SF-36, Perceived Stress Scale, and the ACTG Adherence Baseline & Follow-Up Questionnaire). The primary endpoint is the change in anxiety and depression scores (HADS-A and HADS-D) from baseline to 3 months. All secondary endpoints will be assessed at baseline, 3 months, 6 months, and 12 months.

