### Primary outcome measure

#### Hospital anxiety and depression scale (HADS).

In 1983, Zigmond and Snaith created the widely used Hospital Anxiety and Depression Scale (HADS), a self-assessment tool, to identify whether patients in non-psychiatric hospitals or clinics, potentially or probably have anxiety disorders or depression. The scale comprises 14 items divided into two subscales: the HADS-A (Anxiety Subscale), with 7 items assessing anxiety symptoms, and the HADS-D (Depression Subscale), with 7 items assessing depression symptoms. The scale has cut-off points for classifying symptom severity: 0–7 is normal, 8–10 is borderline abnormal (mild), and 11–21 is abnormal (moderate to severe). This tool has strong internal consistency for both measures in HIV population, with a Cronbach’s alpha of 0.83 and 0.84 for the anxiety subscale and depression subscale respectively [28].

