### Randomization

Once consented, and after baseline assessment, eligible participants will be randomized (1:1 allocation ratio) using permuted block randomization. A priori, a computer-generated randomization schedule prepared by an independent statistician in randomized, permuted block lengths. Variable block sizes (4, 6, or 8) are used to ensure group balance throughout the study and minimize predictability. Multiple small block sizes are chosen to limit the risk of anticipating the next group assignment while ensuring overall group balance throughout the trial. Allocation numbers will be concealed in opaque sealed envelopes, only accessible to the study staff. The envelopes will be opened after informed consent and baseline assessment. Blinding will be maintained for the outcome assessor and statistician analyzing the data, who will be unaware of group assignments. Baseline evaluations will be done by the nursing staff, and then the randomization will be done by separate C.I.M.R. staff who will not be part of the assessment or intervention.

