The present trial possesses several methodological strengths. It employs a randomized design to ensure balanced allocation between groups and to minimize allocation bias and predictability throughout the study. Assessments of outcomes are planned up to one-year post-randomization, enabling the evaluation of both immediate and sustained effects of the yoga intervention. The longer follow-up period will provide valuable insights into the durability of psychological and behavioral benefits over time. Additionally, the use of the TIDieR-Rehab (Template for Intervention Description and Replication for Rehabilitation) checklist ensures comprehensive documentation of the yoga intervention, thereby promoting clarity, transparency, and reproducibility of the study protocol.

A potential limitation of the trial lies in the reliance on self-reported measures for key outcomes such as depression, anxiety, stress, and quality of life. These subjective assessments may introduce recall or response bias; however, standardized and validated instruments will be used to mitigate these effects as far as possible.

If proven effective, the findings from this trial could mark a significant shift in HIV management from a primarily biomedical focus toward a more holistic, patient-centered approach that integrates mental health and overall well-being. Understanding the mechanistic physiological effect of yoga in the disease’s outcome may provide a strong rationale for systematically incorporating structured yoga practices into routine HIV care settings, ultimately enhancing both treatment adherence and quality of life among people living HIV.

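### The trial is labelled blinded-endpoint, but HADS and the other questionnaires are rated by participants who know their arm; the label and the stated limitation should say so.

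*Protocol article*

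**What the plan says.** The label appears twice: in the abstract, which describes a "two-arm, parallel-group, open-label, blinded-endpoint, single-center, randomized controlled trial", and under Trial design, where the study is again a "two-arm, parallel, prospective, randomized, open-label, blinded-endpoint trial".

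Under Description of the outcome measures: "The primary endpoint is the change in anxiety and depression scores (HADS-A and HADS-D) from baseline to 3 months". The HADS section describes the scale as "a self-assessment tool, to identify whether patients in non-psychiatric hospitals or clinics" may have an anxiety or depressive disorder. The secondary questionnaires (PSS, WHOQOL-HIV BREF, SF-36, the single-item adherence question and ACTG-AQ) are also answered by the participant.

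The Randomization section states who is blinded: "Blinding will be maintained for the outcome assessor and statistician analyzing the data, who will be unaware of group assignments". Participants are not listed, and could hardly be, since one arm does yoga and the other a prescribed brisk walk.

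The Discussion gives as a potential limitation the "reliance on self-reported measures for key outcomes such as depression, anxiety, stress, and quality of life". It mentions recall and response bias, and answers that "standardized and validated instruments will be used to mitigate these effects as far as possible".

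**The concern.** In an open-label trial, a blinded endpoint means that whoever determines the outcome does not know the allocation. For a self-rated scale that person is the participant. The design therefore states a property for its primary endpoint that the endpoint cannot have in this comparison.

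What is at stake is how a HADS difference will be read. A participant who knows the arm may rate symptoms according to what he or she expects of yoga or of walking. A between-arm difference may then combine an effect of yoga with expectation and reporting effects. A reader who takes the label at face value would think this possibility had been designed out.

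The limitation in the Discussion does not repair this. It concedes response bias in general, does not connect it with knowledge of allocation, and offers only validated instruments in reply. Validation shows that a scale measures its construct reliably. It does not stop people who know their treatment from answering differently.

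**Working it through.** **Step 1. Who produces each outcome, and is that person blinded?**

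| Outcome | Who produces the value | Blind to arm? |
|---|---|---|
| HADS-A, HADS-D (primary) | Participant | No |
| PSS, WHOQOL-HIV BREF, SF-36 | Participant | No |
| Self-reported adherence, ACTG-AQ | Participant | No |
| Blood pressure, waist-hip ratio | Staff | Can be, under the Randomization section |
| Statistical analysis | Statistician | Yes, as stated |

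No clinician-rated or adjudicated version of the primary outcome is described. The label can hold for the staff-measured items, and none of these is primary.

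**Step 2. Reproduce the plan's sample size.** Inputs from Sample size calculation: mean difference 1.54, SD 3.38, two-sided alpha 0.05, power 80%, 1:1 allocation, 20% attrition.

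- d = 1.54 / 3.38 = 0.456 (stated as 0.455).
- The two-sample t-test with d = 0.455 needs 76.8, so 77 per arm and 154 in total, with power 80.1%. This agrees with the plan.
- 154 / 0.80 = 192.5, against 192 stated. The half-participant is immaterial here.

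**Step 3. Precision, as an illustration.** Assume that the SD of 3.38 applies to one HADS subscale (the section does not name the scale), 77 per arm are analysed, and there is no baseline adjustment.

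- SE = 3.38 × sqrt(2/77) = 0.545.
- Half-width = t(0.975; 152) × SE = 1.976 × 0.545 = 1.08 points.
- The planned ANCOVA would be tighter. With an assumed baseline-outcome correlation of 0.5, the factor is sqrt(1 − 0.25) = 0.866, and 1.076 × 0.866 = 0.93 points.

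**Step 4. What a reporting bias would do, if there were one.** The documents give no size for it, so a range is assumed. With no true effect and bias b, the chance of a significant result on one subscale (normal approximation) is Φ(b/SE − 1.96) + Φ(−b/SE − 1.96), with SE = 0.545.

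| Assumed bias b (points) | b / 1.54 | Chance of a significant result |
|---|---|---|
| 0 | 0% | 5% |
| 0.25 | 16% | 7% |
| 0.50 | 32% | 15% |
| 0.75 | 49% | 28% |
| 1.00 | 65% | 45% |

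Blinding the statistician, or the staff who collect the forms, does not alter this table, because b is already in the participant's answer.

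**The case against.** The strongest reply is that nothing is hidden. Open-label stands in the same phrase as the label, the Randomization section says exactly who is blinded, and the Discussion lists self-report as a limitation and claims mitigation only as far as possible. A careful reader can work out that HADS is self-rated by unblinded people. This stands as far as it goes: the fault is an inaccurate label and an incomplete limitation, not concealment. It does not make the label correct for the primary endpoint.

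Secondly, a reader might infer that the blinding is worthless for HADS. The documents do not support that. A blinded assessor can still avoid prompting, selective clarification and scoring errors, and a blinded statistician protects the analysis. The article does not say whether follow-up forms are completed alone or with help, so the assessor's role cannot be assumed to be trivial.

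Thirdly, a reader might infer that yoga participants receive more attention, from the 36 supervised sessions and the calls every 15 days. The calls appear in a checklist that describes only the yoga arm, and details of the control arm are referred to S1 Annexure, which is not shown. An imbalance in contact is not established. The control is also active, three times a week for 12 weeks, which may lessen differences in expectation, although it does not blind anyone.

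Lastly, the figures are weak as evidence. The scale behind 1.54 and 3.38 is not named, the 1.08 half-width ignores the planned baseline adjustment, and every bias size is assumed. That is accepted, and they serve only as illustration.

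**Conclusion.** The point holds as one of labelling and interpretation. The protocol states a blinded endpoint, while its primary endpoint and its questionnaire-based secondary outcomes are rated by participants who know their arm. The protection that is missing is against bias in the participant's own rating. Protection against staff prompting, scoring and analysis bias remains, as does possible blinding of the physical measurements. This conclusion rests on the article's own description of HADS, its list of who is blinded and the nature of the two interventions. It does not depend on any calculation.

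On size, the unadjusted half-width is about 1.08 points, or about 0.93 if a baseline correlation of 0.5 is assumed. It is tempting to subtract, 1.54 − 1.08 = 0.46, and conclude that a reporting bias of that size would take the planned effect to the edge of significance. The documents do not support this as a threshold: the margin moves with the baseline adjustment, the scale is an assumption, and nothing indicates how large reporting bias would be, or that it will occur.

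**What to change.** 1. In the abstract and under Trial design, either drop blinded-endpoint or restrict it to the named staff roles (outcome assessor, statistician) and the staff-measured outcomes.
2. State that HADS, PSS, WHOQOL-HIV BREF, SF-36, self-reported adherence and ACTG-AQ are participant-reported and unblinded.
3. In the Discussion, name lack of participant blinding as a source of response bias that validated instruments do not remove, and say that a HADS difference may include expectation and reporting effects.

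The cost is a few sentences and a slightly more modest claim about rigour. Sample size, primary model, alpha and data collection are unchanged. A separate tipping-point analysis is not needed: a constant reporting shift simply moves the estimate and its interval, which a reader can do from the published result. The delta-adjusted analysis already planned concerns missing data and does not address bias in observed scores. No change to contact schedules or to the registry entry follows from this point.

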**Discussion:**

The findings of this RCT will help shed light on yoga intervention to address the psychosocial dimensions of HIV. If shown to be effective, yoga as an adjunct intervention may promote a transition in HIV care from a predominantly biomedical framework to a holistic, patient-centered approach encompassing mental health and overall well-being. The study is approved by Institute Research Board Ethics (AIIMSA2969/03.01.2025, RP-46/25, OP-16/02.05.25, OP-18/05.12.2025) and is registered at Clinicaltrials.gov (CTRI/2025/03/081645). CTRI Link- https://www.ctri.nic.in/Clinicaltrials/pmaindet2.php?EncHid=MTIyNjUx&Enc=&userName=HIV,%20Yoga

## Introduction

Human immunodeficiency virus (HIV), is a retrovirus responsible for acquired immunodeficiency syndrome (AIDS), and remains a significant global public health concern [1]. As of 2024, an estimated 40.8 million individuals were living with HIV worldwide, with 630,000 deaths attributed to AIDS-related causes [2]. In India, HIV prevalence among adults is approximately 0.22% (0.17–0.29%) [3].

HIV infection triggers complex innate and adaptive immunological reactions. Despite the activation of CD4 and CD8 T cells, these defense mechanisms are inadequate to eradicate the virus [2,4]. Currently, there is no definitive cure for HIV [5]. The effective ART/HAART (highly active antiretroviral therapy) is the cornerstone treatment for HIV infection, which acts on the suppression of viral replication, thereby preserving the immune function and prolonging survival, thus transforming HIV into a chronic condition [6–8]. If left untreated, HIV may progress to acquired immunodeficiency syndrome (AIDS), marked by severe immune suppression and development of HIV-related malignancies or opportunistic infections [9].

HIV initiates a cascade of physiological disturbances, including chronic stress, heightened inflammation, oxidative damage, and disruptions in monoamine neurotransmission that collectively contribute to depression by altering key biological pathways, particularly those described by the cytokine hypothesis [10] and the monoamine neurotransmitter hypothesis [11].

Yoga exerts modulatory effects through multiple converging biological pathways. It promotes neuroendocrine balance by lowering cortisol levels and enhancing parasympathetic activation [12,13]. Yoga also modulates immune function by reducing pro-inflammatory cytokines such as TNF-α and IL-6 while increasing anti-inflammatory markers like IL-10 [14]. Besides it restores neurotransmitter homeostasis by elevating serotonin, dopamine, and GABA levels [15]. Additionally, yoga enhances neuroplasticity via upregulation of BDNF [10] and strengthens emotional regulation through mindfulness-based practices and controlled breathwork. By targeting the same physiological pathways disrupted by HIV, yoga offers a biologically plausible and integrative complementary therapy to mitigate depressive symptoms in people living with HIV.

Evidence suggests that a short yoga-based intervention, lasting 10 days, significantly reduced IL-6 and TNF-α levels while increasing β-endorphin levels in patients with stress and inflammation [16]. Similarly, an 8-week mindfulness meditation program improved CD4 + T lymphocyte counts in HIV-1-infected individuals [17]. Yoga also showed improvement in clinical insight and medication adherence in schizophrenia patients [18]. In People living with HIV (PLHIV) receiving combination ART, yoga resulted in a reduction in resting systolic and diastolic blood pressure compared to standard care [19]. Moreover, Yoga significantly improved functional capacity and health-related quality of life (HRQL) compared to standard care in HIV-seronegative population with heart disease, stroke, and COPD [20]. According to a recent meta-analysis, yoga intervention significantly improved perceived stress (k = 3), positive affect (k = 3), and anxiety (k = 2) compared to non-yoga control conditions in PLHIV. No significant changes were found for depression and quality of life (k = 2), potentially due to limited sample sizes, pilot study designs and lack of long-term follow-up [21]. Given the current evidence and limitations of existing research, there remains a paucity of data supporting the effect of yoga-based interventions in PLHIV. There is a clear need for a well-structured yoga-based intervention study that may help improve mental health status, quality of life, and medication adherence of PLHIV.

### Rationale

People living with HIV (PLHIV) often experience significant psychological challenges such as anxiety, depression, and stress, stemming from the chronic and progressive nature of the disease. These challenges are further exacerbated by stigma, discrimination, and social isolation, which collectively impair mental health, quality of life (QoL), and medication adherence. Understanding the biological mechanisms underlying HIV-associated psychological disturbances is therefore essential.

HIV infection directly impacts key physiological pathways associated with depression, including dysregulation of the hypothalamic–pituitary–adrenal (HPA) axis, [22] activation of pro-inflammatory cytokine pathways, [23] and alteration in monoamine neurotransmitter systems [24]. Based on these neurophysiological evidences, yoga holds potential in mitigating the psychological effects of HIV infection in PLHIV. However, its application requires a customized, standardized, and validated approach to ensure consistency and effectiveness.

Despite growing evidence supporting the benefits of yoga for psychological well-being and QoL across diverse populations, substantial gaps remain in the context of HIV. Firstly, marked heterogeneity in the yoga forms (e.g., Hatha, Integrated, Sudarshan Kriya) and their durations across existing studies limits understanding of which specific practices are most effective for improving psychological outcomes and quality of life (QOL). Secondly, many existing studies are pilot trials with small sample sizes and short follow-up periods, resulting in inconsistent findings and limited generalizability. Importantly, this study is among the first to evaluate the impact of yoga on medication adherence, extending beyond psychological outcomes and quality of life in PLHIV.

### Study objective

The trial aims to assess the effectiveness of yoga therapy as an adjunct therapy on psychological parameters (depression, anxiety, and stress), quality of life, and medication adherence of PLHIV on ART at a tertiary care hospital in AIIMS New Delhi, India.

Research Questions:

What is the effect of yoga therapy as an adjunct therapy on Depression and anxiety scores among people living with HIV (PLHIV) on ART?What is the effect of yoga as an adjunct therapy on Quality of Life among PLHIV on ART?What is the effect of yoga therapy as an adjunct therapy on Perceived Stress among PLHIV on ART?What is the effect of yoga therapy as an adjunct therapy on ART medication adherence among PLHIV on ART?

#### Hypothesis.

The primary hypothesis to be tested is that yoga therapy as an adjunct therapy will lead to a change in depression and anxiety scores among PLHIV on ART therapy as compared to an active control (moderate-to-intensity walk). The secondary hypothesis included that a yoga therapy would lead to changes in all secondary health outcomes and would produce significant changes in medication adherence among PLHIV on ART therapy, as compared to an active control (moderate-to-intense walk).

## Materials and methods

### Trial design

We propose a two-arm, parallel, prospective, randomized, open-label, blinded-endpoint trial with four assessment points: baseline, 3 months, 6 months, and 12 months. The study protocol has been developed in compliance with the Standard Protocol Items: Recommendations for Interventional Trials (SPIRIT) checklist (see S1 SPIRIT Checklist), and the SPIRIT schedule for the study is presented in Fig 1, including the screening, enrolment, and follow-up visit timelines [25]. The CONSORT flow diagram of the study protocol is shown in Fig 2. A visual abstract summarizing the study design is provided in Fig 3. The total study duration is 3 years, including 1 year of follow-up.

